## Abstract

**Background:**

Adaptive thermogenesis, defined as the decrease in the energy expenditure components beyond what can be predicted by changes in body mass stores, has been studied as a possible barrier to weight loss and weight maintenance. Intermittent energy restriction (IER), using energy balance refeeds, has been pointed out as a viable strategy to reduce adaptive thermogenesis and improve weight loss efficiency (greater weight loss per unit of energy deficit), as an alternative to a continuous energy restriction (CER). Following a randomized clinical trial design, the BREAK Study aims to compare the effects of IER versus CER on body composition and in adaptive thermogenesis, and understand whether participants will successfully maintain their weight loss after 12 months.

**Methods:**

Seventy-four women with obesity and inactive (20–45 y) will be randomized to 16 weeks of CER or IER (8x2 weeks of energy restriction interspersed with 7x1 week in energy balance). Both groups will start with 2 weeks in energy balance before energy restriction, followed by 16 weeks in energy restriction, then 8 weeks in energy balance and finally a 12-month weight maintenance phase. Primary outcomes are changes in fat-mass and adaptive thermogenesis after weight loss and weight maintenance. Secondary outcomes include weight loss, fat-free mass preservation, alterations in energy expenditure components, and changes in hormones (thyroid function, insulin, leptin, and cortisol).

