## 1. Introduction

Despite extensive research into lifestyle interventions for weight loss (WL) [1], one of the major challenges for treating obesity is WL maintenance [2], since weight regain rates are high [3]. Lack of long-term adherence to dietary and/or exercise recommendations has been pointed out as the major reason [4], however the existence of compensatory mechanisms in response to a prolonged negative energy balance (EB) may also play a role [5].

A decrease in resting energy expenditure (REE) is expected during a WL intervention due to fat-mass (FM) and fat-free mass (FFM) losses. However, some authors [6–8] showed that these reductions tend to be greater than predicted by WL, a phenomenon called “adaptive thermogenesis” (AT). Then, AT can function as a barrier to WL and contribute to weight regain [9, 10]. Still, some studies reported contrasting findings, as they did not find a significant value for AT even after a considerable WL [11–14]. This can be explained by a large heterogeneity in the methods used to quantify AT, a high variability in study designs, between subjects, and the wide magnitude of WL [15].

Furthermore, its relevance on long-term weight management (WM) has been recently questioned [16], as AT seems to be attenuated or even non-existent [15] after periods of (two to five weeks [16–19]) of weight stabilization.

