Campbell et al. [23] investigated body composition changes in lean resistance trained individuals following a ~25% ER for 7 weeks in conjunction with 4-days/week resistance training, randomized to either IER or CER. IER cycled 5 days of ER with 2 days of EB using carbohydrate refeeds. The authors found that a 2-day carbohydrate refeed preserved FFM, dry FFM and REE during ER, compared to CER in resistance trained individuals. Davoodi et al. [30] compared IER and CER in 74 women with overweight and obesity for a six-week period. IER consisted of 3 cycles of 2 weeks (6-week total), and each cycle included 11 days of ER followed by 3 days of EB. IER was associated with a greater improvement in anthropometric measures, showed a better adherence to the dietary plan and a higher REE by the end of ER period, compared to CER. Byrne at al. [6] examined whether IER improved WL efficiency compared to CER in 51 men with obesity, for a 16-week ER period. IER group cycled 14 days of ER followed by 14 days of EB (30 weeks in total), with an ER of 33% in both IER and CER groups. The authors found a greater WL and fat loss with IER, and reported AT only for the CER group (~209 kJ/d) after a weight loss of ~8,4% of the initial weight, despite a greater weight loss in the IER group ~12,9%. As only men were included in the Byrne et al. study [6], there is a need to study the effects of a similar intervention in women. Furthermore, considering that the compensatory metabolic responses following ER and WL need a period of 7-to-14-days post-WL to be reversed [6, 25], and in order to maximize the ER/EB days´ ratio, another IER pattern should be considered. To our knowledge, this will be the first RCT comparing CER with IER (cycling 14 days of ER followed by 7-day EB periods), in women with obesity.

Pending this approach as a potential opportunity for obesity’s treatment, this paper describes the protocol for a RCT, targeting to evaluate the effects of an IER, interspersing 14 days of ER with 7 days of EB, comparing to a CER. The primary aim of the trial is to assess whether IER will determine a greater FM loss and a reduced AT during WL and after 12-month maintenance, avoiding weight regain, compared to CER, in women with obesity and inactive. Secondary outcomes include WL, retention of FFM, alterations in EE components, and AT plasma-derived indices (thyroid function, insulin, leptin and cortisol).

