#### 3.5.1. Power sample calculation

For sample and power calculations, this study is powered based on changes in total body fat assessed by DXA. Considering a type I error of 5% and a power of 95% to detect differences at the dependent variable, with a statistical significance and an effect size of 0.93 (differences in FM (kg) were considered following Byrne et al. results [6]), a total of 26 participants per group will be needed (using GPower software version 3.1.9.6). Considering a 30% drop-out rate [6] throughout the study, we will recruit 74 participants (37 in each group).

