## 4. Discussion

This RCT aims primarily to evaluate the effects of an IER, interspersing 14 days of ER with 7 days of EB, on body composition (body weight, FM and FFM), and more specifically on AT, during WL and WM phase. It also aims to understand whether participants from both groups (IER and CER) will successfully maintain their WL 12 months after completion of the intervention.

Secondary objectives of this study are the following: (i) to compare the effects of IER and CER on WL, FM loss, and preservation of FFM and REE during the intervention phase; (ii) to determine which group is more successful in the 12-month WM phase and in improving body composition profile (higher FM loss with best preservation of FFM); (iii) to analyze if AT is maintained during WM phase; (iv) to analyze the impact of AT in WM phase, regarding the hormonal adaptation (plasma hormones: cortisol, insulin, leptin, thyroid free T3 and T4).

A 5% WL has been pointed out to be enough to improve metabolic parameters (glycemic measures and triglycerides, blood pressure, HDL and LDL cholesterol) and is currently a standard goal in WL interventions [65]. Nevertheless, a greater reduction of 10% or more can lead to maximal health benefits, reducing many of the comorbidities associated with obesity [66, 67]. In fact, according to Wing and Hill [68], successful WL maintainers should be defined as “individuals who have intentionally lost at least 10% of their body weight and kept if off at least 1 year”. With The BREAK Study we expect to find a clinically significant weight loss [69] of 10% in both groups, considering the length of the ER intervention, and the magnitude of ER [70].

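### The article defines its primary outcome in conflicting ways and powers only fat mass, so which comparison decides the trial is not fixed; the visit in the adaptive thermogenesis formula is also unclear

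*Protocol article*

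**What the plan says.** **Abstract, Methods.** "Primary outcomes are changes in fat-mass and adaptive thermogenesis after weight loss and weight maintenance". The next sentence begins "Secondary outcomes include weight loss, fat-free mass preservation".

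**Section 1, Introduction.** The primary aim is "to assess whether IER will determine a greater FM loss and a reduced AT during WL and after 12-month maintenance, avoiding weight regain". Weight loss and FFM are again secondary.

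**Section 4, Discussion.** The main aim is the effect of intermittent energy restriction (IER) against continuous energy restriction (CER) "on body composition (body weight, FM and FFM), and more specifically on AT, during WL and WM phase". Secondary objective (i) is then "to compare the effects of IER and CER on WL, FM loss, and preservation of FFM and REE during the intervention phase", objective (ii) covers body composition over the 12-month maintenance phase, and objective (iii) is "to analyze if AT is maintained during WM phase".

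**Section 3.5, Statistics.** One two-tailed 5% level is given for the whole analysis. The mixed model covers all visits, and the contrasts between groups are defined between two generic times.

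**Section 3.5.1.** "this study is powered based on changes in total body fat assessed by DXA". No visit is given.

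**Section 3.2.1.** AT is the measured-minus-predicted resting energy expenditure at the end of the intervention, less the same difference at baseline.

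**The concern.** A confirmatory trial needs one identifiable answer to the question of which result decides it. Here FM is primary in the Abstract and Introduction, and both primary and secondary in the Discussion. Body weight and FFM are secondary in the Abstract and primary in the Discussion. AT during maintenance is primary in the Abstract and is listed again as a secondary objective in the Discussion.

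Two things are at stake. If success on any one primary comparison is enough, the chance of a false positive claim exceeds 5%. If every primary comparison must succeed, the power calculation, which concerns FM alone, does not describe the trial's chance of success. The article does not say which rule applies.

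The AT visit matters for a related reason. The Introduction cites evidence that AT may not persist once weight has been stable for some weeks ("as AT seems to be attenuated or even non-existent"), so the answer could depend on which visit the formula means.

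**Working it through.** **1. The statements side by side**

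| Place | FM | AT | Body weight | FFM |
|---|---|---|---|---|
| Abstract | primary, two stages | primary, two stages | secondary | secondary |
| Introduction | primary, two stages | primary, two stages | regain within the primary aim; weight loss secondary | secondary |
| Discussion, main aim | primary, both phases | primary, both phases | primary, both phases | primary, both phases |
| Discussion, secondary objectives | (i), (ii) | (iii) | (i), (ii) | (i), (ii) |
| Section 3.5.1 | powered, visit not named | not powered | not powered | not powered |

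The Abstract gives 2 outcomes × 2 stages = 4 comparisons. The Discussion, read literally, gives 4 × 2 = 8.

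**2. The plan's own figure**

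Inputs (Section 3.5.1): standardised effect 0.93, type I error 5%, power 95%, 26 per group.

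n per group = 2(z_α + z_β)² / d², with d² = 0.93² = 0.8649.
- One-sided 5%: 2 × (1.645 + 1.645)² / 0.8649 = 25.03, so 26. The exact t-test also gives 26, with power 95.2%.
- Two-sided 5%: 2 × (1.960 + 1.645)² / 0.8649 = 30.05, so 31. The exact t-test gives 32, and 26 per group has power 90.8%.

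The stated 26 is therefore reproduced only with a one-sided test. Under the two-tailed level of Section 3.5, power for FM is about 91%.

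**3. Error rate if any one significant primary result counts as success**

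- Four comparisons, independent: 1 − 0.95⁴ = 18.5%, or 3.7 times 5%. The bound under any dependence is 4 × 5% = 20%, or 4 times.
- Four comparisons, simulated with assumed correlations of 0.5-0.8 between stages and 0-0.5 between outcomes: about 14-17%, or 2.8-3.5 times.
- Eight comparisons, independent: 1 − 0.95⁸ = 33.7%, or 6.7 times.
- Eight comparisons, simulated with body weight equal to FM plus FFM and assumed correlations of 0-0.7 between stages: about 23-29%, or 4.6-5.8 times.

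The correlations are assumptions; the article gives none.

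**4. If all primary comparisons must succeed**

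The false positive rate cannot exceed 5%. Power cannot be computed, because no effect size is given for AT or for the maintenance stage. As an illustration, if each of four tests had 95% power, joint power could be as low as 1 − 4 × 0.05 = 80%, and would be 0.95⁴ = 81.5% under independence.

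**5. The AT visit**

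- Towards the 7th visit: Section 2.1 describes a three-phase intervention whose third phase is eight weeks of energy balance, and Section 2.8.1 ends the intervention phase at the 7th visit. In the time points under Fig 1 this is t26.
- Towards the end of energy restriction (t18): Section 2.5 speaks of the weight-loss intervention and then shortens the term to the intervention alone, and the Abstract asks for AT after weight loss.
- Section 3.2.1 also computes predicted expenditure at each time point, so AT can be derived at either visit.

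The text does not settle the question.

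**The case against.** The strongest reply has four parts.

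- **Multiplicity may be dealt with elsewhere.** A testing order, an adjustment or a success rule commonly sits in a statistical analysis plan, which is not shown. This stands: the absence of such a rule is no finding. A reader might also infer that Section 3.5 tests every contrast unadjusted, but it states only a general level. What an unseen plan cannot do is make the article's own statements agree.
- **The inflation depends on a rule that the article never states.** The Introduction can be read as requiring both greater FM loss and reduced AT. This stands, and the error figures are conditional on it.
- **The Discussion sentence is an aim, not an outcome list.** The Abstract is the explicit outcome statement and the Introduction largely agrees with it. A reader might infer an error of up to seven times 5%. That needs eight independent tests, whereas body weight is roughly FM plus FFM and the stages are repeated measures on the same women. The Abstract's four tests cannot exceed four times.
- **AT is available at every visit.** This also stands. A reader might infer that AT is to be tested only at the 7th visit, where none is expected. The wording is ambiguous, the Introduction reports that evidence cautiously alongside contrasting findings, and objective (iii) treats persistence as an open question.

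**Conclusion.** The contradiction in primary outcomes is in the text and holds without any assumption. Its consequence depends on a success rule that the article does not give:

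- Any one success suffices: familywise error of 18.5% under independence for the Abstract's four comparisons, and about 14-17% under the assumed correlations, so roughly 3-4 times 5%.
- The larger figures (23-29%, or 33.7% if independent) apply only if the Discussion's eight comparisons are taken as the primary set.
- All must succeed: error is at most 5%, but the stated 95% power does not describe the trial.

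The AT formula's visit is ambiguous, which needs clarifying; the documents do not show that the wrong visit was chosen.

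**What to change.** 1. Make the Abstract, Introduction and Discussion agree on one primary set, and remove from the secondary objectives whatever is kept as primary.
2. Name one primary outcome: the change in DXA fat mass from the pre-restriction scan to the end of 16 weeks of energy restriction (t18), tested two-sided at 5%. DXA is done at only five of the eight visits and Fig 2 is not shown, so confirm against it which pre-restriction visit has a scan and that t18 has one.
3. Test AT at t18, then FM at t78, then AT at t78, in a pre-stated fixed order in which each test is confirmatory only if the one before it is significant. Alternatively, label these three secondary.
4. State the visit in the AT formula of Section 3.2.1.
5. Report power for FM as about 91% at 26 per group, two-sided.

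**Cost.** No added participants are needed for multiplicity, because the full 5% stays on FM. By comparison, splitting 5% equally over four tests (1.25% each, two-sided) would leave about 77% power for FM at 26 per group and would need 42 per group for 95%. The price of the fixed order is that an early non-significant result blocks confirmatory claims on later outcomes. Putting FM ahead of AT is a choice for the team, since the Discussion stresses AT. Section 2.1 says that the trial was registered before recruitment, which Section 3.5.2 dates from January 2022. The change therefore needs a dated amendment, with the registered outcomes brought into line, before any unblinded comparison of the groups.

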**Discussion:**

We anticipate that The BREAK Study will allow us to better understand adaptive thermogenesis during weight loss and weight maintenance, in women with obesity. These findings will enable evidence-based decisions for obesity treatment.

**Trial registration:**

ClinicalTrials.gov: NCT05184361.

## 1. Introduction

Despite extensive research into lifestyle interventions for weight loss (WL) [1], one of the major challenges for treating obesity is WL maintenance [2], since weight regain rates are high [3]. Lack of long-term adherence to dietary and/or exercise recommendations has been pointed out as the major reason [4], however the existence of compensatory mechanisms in response to a prolonged negative energy balance (EB) may also play a role [5].

A decrease in resting energy expenditure (REE) is expected during a WL intervention due to fat-mass (FM) and fat-free mass (FFM) losses. However, some authors [6–8] showed that these reductions tend to be greater than predicted by WL, a phenomenon called “adaptive thermogenesis” (AT). Then, AT can function as a barrier to WL and contribute to weight regain [9, 10]. Still, some studies reported contrasting findings, as they did not find a significant value for AT even after a considerable WL [11–14]. This can be explained by a large heterogeneity in the methods used to quantify AT, a high variability in study designs, between subjects, and the wide magnitude of WL [15].

Furthermore, its relevance on long-term weight management (WM) has been recently questioned [16], as AT seems to be attenuated or even non-existent [15] after periods of (two to five weeks [16–19]) of weight stabilization.

Continuous energy restriction (CER), meaning a constant daily energy restriction (ER) according to individual’s energy requirements, is the most common nutritional strategy for WL [20, 21]. However, some concerns have been pointed out to this strategy, since the behavioral, metabolic and endocrine adaptive responses it causes can compromise therapeutic adherence, undermining WL and WM [21–23]. These adaptive responses include an increased drive to eat, a reduced physical activity (PA) or energy cost of PA, a reduced energy expenditure (EE), and hormonal effects that facilitate the accumulation of adipose tissue and loss of lean tissues [24]. ER is associated with a reduction in thyroid hormones secretion (T3 and T4), variations in appetite-regulating hormones (decreased leptin, peptide YY, and increased ghrelin), variations in steroid hormones (increased cortisol), reduced insulin and testosterone, that all together influence EE, satiety and body composition [25, 26]. Simultaneously, some behavioral adaptations as a response to negative EB may occur, such as increasing sedentary behavior and/or decreasing light PA, more consistently observed in diet-only induced WL [26, 27].

Intermittent energy restriction (IER), which consists in interspersing periods of ER with periods of EB (the “refeed” or “diet breaks”), has been suggested as an alternative to CER [22]. The inclusion of periods of neutral EB is expected to attenuate adaptive responses to ER and WL in some regulatory hormones, which play a role in WL, satiety and REE [22, 24].

According to literature, there are 8 randomized clinical trials (RCT) comparing CER with IER in people with overweight/obesity, that achieved EB in the refeeding phases [6, 22, 23, 28–32]. Of these, only three resulted in a greater WL with IER [6, 23, 30]. Variability in study design in these 8 RCT may have contributed to the different findings, favoring IER or not in comparison with CER. The study design differed in the duration of the intervention, the pattern of intermittency (days of ER vs. EB), the severity of calorie restriction, the food provision, the exercise recommendations, the adherence to the intervention, the sample size, and the baseline characteristics of the study population (sex and BMI).

Campbell et al. [23] investigated body composition changes in lean resistance trained individuals following a ~25% ER for 7 weeks in conjunction with 4-days/week resistance training, randomized to either IER or CER. IER cycled 5 days of ER with 2 days of EB using carbohydrate refeeds. The authors found that a 2-day carbohydrate refeed preserved FFM, dry FFM and REE during ER, compared to CER in resistance trained individuals. Davoodi et al. [30] compared IER and CER in 74 women with overweight and obesity for a six-week period. IER consisted of 3 cycles of 2 weeks (6-week total), and each cycle included 11 days of ER followed by 3 days of EB. IER was associated with a greater improvement in anthropometric measures, showed a better adherence to the dietary plan and a higher REE by the end of ER period, compared to CER. Byrne at al. [6] examined whether IER improved WL efficiency compared to CER in 51 men with obesity, for a 16-week ER period. IER group cycled 14 days of ER followed by 14 days of EB (30 weeks in total), with an ER of 33% in both IER and CER groups. The authors found a greater WL and fat loss with IER, and reported AT only for the CER group (~209 kJ/d) after a weight loss of ~8,4% of the initial weight, despite a greater weight loss in the IER group ~12,9%. As only men were included in the Byrne et al. study [6], there is a need to study the effects of a similar intervention in women. Furthermore, considering that the compensatory metabolic responses following ER and WL need a period of 7-to-14-days post-WL to be reversed [6, 25], and in order to maximize the ER/EB days´ ratio, another IER pattern should be considered. To our knowledge, this will be the first RCT comparing CER with IER (cycling 14 days of ER followed by 7-day EB periods), in women with obesity.

Pending this approach as a potential opportunity for obesity’s treatment, this paper describes the protocol for a RCT, targeting to evaluate the effects of an IER, interspersing 14 days of ER with 7 days of EB, comparing to a CER. The primary aim of the trial is to assess whether IER will determine a greater FM loss and a reduced AT during WL and after 12-month maintenance, avoiding weight regain, compared to CER, in women with obesity and inactive. Secondary outcomes include WL, retention of FFM, alterations in EE components, and AT plasma-derived indices (thyroid function, insulin, leptin and cortisol).

## 2. Methods

### 2.1. Study design

The BREAK study is a RCT (allocation ratio of 1:1) that will be performed in adult women with obesity, randomly divided in 2 parallel groups: 1) CER and 2) IER. This study will include a three-phase intervention:

2 weeks of neutral EB;Active WL phase, where both groups will undergo 16 weeks of ER: CER—16 weeks of continuous ER; IER—2 weeks of ER interspersed with 1 week in EB, leading to a total of 23 weeks. IER length is 7-week longer than CER due to the 7x1-week of neutral EB, to maintain the same magnitude of ER in both interventions;8 weeks in neutral EB.

Participants will also be evaluated 12 months after the 3rd phase, to determine WL maintenance success. SPIRIT diagram is presented in Fig 1.

